### Remote consenting process

Given the size and large geographic area (all 50 U.S. states and the District of Colombia) for which we are recruiting and enrolling participants, the use of electronic informed consent (IC) became a vital component to the study. Electronic informed consent is defined by the FDA as the use of electronic systems and processes that may employ multiple electronic media, such as text, graphics and videos, to convey information related to the study and obtain and document informed consent (http://www.fda.gov/downloads/drugs/guidancecomplianceregulatoryinformation/guidances/ucm436811.pdf).

Our biggest challenge was ensuring that the person signing the IC is the same as the person completing the study procedures. We accomplished this by requiring all participants to create a unique username and password that must be used to confirm their identity before signing the IC and before completing each study survey. To ensure that consent is truly informed, we created a series of comprehension questions that the participant must answer correctly before being allowed to sign the IC. The IC was delivered to study participants by email using the survey tools in REDCap. All other aspects of the FDA draft guidance were followed, including allowing the participant the ability to print a copy of the IC and call the study coordinator for questions (http://www.fda.gov/downloads/drugs/guidancecomplianceregulatoryinformation/guidances/ucm436811.pdf).

### Study interventions

All participants receive online genetic education, including a 5-min pre-test educational video and an online results report. The video provides an explanation of hereditary cancer, inheritance patterns, associated cancer risks, and an overview of the possible results. Participants randomized to receive pre-test telephone counseling are prompted to schedule their telephone appointments online and will complete telephone counseling in addition to the online genetic education. The usual content of pre- and post-test genetic counseling for hereditary cancer risk has been well described [20, 21]. Following these standard guidelines, a genetic counseling outline was created by the study team and is followed by the board-certified genetic counselors involved in the study to guarantee consistency in counseling and ensure standardization for the purposes of the study (Table 4).

**Table 4 Tab4:** Genetic Counseling Outline

Pre-Test Genetic Counseling	
• Review/verification of the family history provided in the online survey	
• Review the basics of hereditary cancer *(incidence, inheritance pattern, define genes & mutations)*	
• Review the benefits and limitations of genetic testing	
• Briefly review the cancer risks	
• Review result possibilities and their implications	
• Briefly discuss the benefits and limitations of GINA	
• Confirm that participant would like to move forward with testing	
• Assess for distress throughout the session using psychosocial training.	
• Documentation of the session and amount of time spent on the phone	
Post-Test Genetic Counseling	
• Verify the participant’s continued interest in receiving genetic test results and encourage them to follow along with their results online	
• Provide genetic test results	
• Review implications of test results for the participant and family members	
• Assess the response of individual to the information provided	
• Allow time for questions or voicing of concerns	
• Provide phone number for contact if needed and information for local GC	
• Assess for distress throughout the session using psychosocial training.	
• Document the session and the amount of time spent on the phone	

### Statistical considerations

We employ a non-inferiority design with a non-inferiority margin of 4 points, as suggested by Schwarz et al. (2014), for the difference in IES score between the control arm and each of the other three study arms at 3 months post-result disclosure.

We are enrolling 5200 eligible women with a goal of 3000 completing genetic testing. We expect that around 85% (*n* = 4400) of those who consent to participate will complete the baseline questionnaire and then be randomized. Of these, we will enroll around 750 subjects with a known familial mutation into the cascade group, with the remaining 3650 subjects, who have an increased likelihood of carrying a deleterious mutation in an ovarian cancer predisposition gene based on personal and family history of disease, as the group of interest for our primary analysis. We expect that 65% (*n* = 2375) of the 3650 participants with personal and/or family history of disease will follow through with providing a saliva sample for analysis, with 75% of those subjects completing the study through the 3 month assessment (*n* = 1780), which equates to about 450 participants on each of the four study arms.

Each of the three experimental study arms will be compared to the control study arm using a one-sided t-test, with the null hypothesis for each of the three tests that the mean stress score in the experimental arm is more than 4 points above the mean stress score in the control arm. A one-sided significance level of 0.025 is targeted across all three tests, resulting in a Bonferroni-corrected significance level of 0.0083 for each test. The sample size was chosen to achieve 93% power for each test, assuming a standard deviation in the scores of 15.3 based on Schwartz et al., yielding an overall power of 80%.

Our secondary outcome is the “completion rate”, defined as a participant progressing through the entire process from pre-test genetic education/counseling to receiving their test results and post-test genetic education/counseling. We will test two null hypotheses regarding the completion rate: that the completion rate for the participants receiving only online genetic education before testing (Arms A and B) is more than 6% less than it is for participants who were randomized to receive telephone genetic counseling before testing (Arms C and D), and that the completion rate for the participants receiving only online genetic education after testing (Arms A and D) is more than 6% less than it is for participants who were randomized to receive telephone genetic counseling after testing (Arms B and D). This 6% non-inferiority margin is more conservative than the 7.5% margin used by Schwartz et al. [5].

In addition to testing our primary and secondary hypotheses, we will summarize for each study arm the key outcomes related to cognition, affect and behavior, and the changes in scores from baseline. We will also use regression models to model the scores (and changes in the scores from baseline) as a function of study arm, risk group, and other covariates.

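### Single-step Bonferroni for three comparisons with one shared control is valid, but Holm gives more power at the same error rate: about 93% rather than 85% to show all three arms non-inferior

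*Protocol article*

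**What the plan says.** All of this is in the protocol article under Statistical considerations, except where noted.

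- Comparisons: "Each of the three experimental study arms will be compared to the control study arm using a one-sided t-test". The control is Arm C in every test.
- Margin: "We employ a non-inferiority design with a non-inferiority margin of 4 points".
- Error rate: "A one-sided significance level of 0.025 is targeted across all three tests", "resulting in a Bonferroni-corrected significance level of 0.0083 for each test".
- Power: "The sample size was chosen to achieve 93% power for each test", "assuming a standard deviation in the scores of 15.3", "yielding an overall power of 80"%.
- Size: 1780 women evaluable at 3 months, "which equates to about 450 participants on each of the four study arms".
- The Methods paragraph of the abstract states that randomization is equal across the four arms.

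The article mentions no step-down rule and no correlation between the three tests. It does not define overall power or show how the 80% was obtained.

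**The concern.** Two separate matters sit in one paragraph of the article.

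The first is the procedure. Single-step Bonferroni holds all three tests at 0.0083 whatever the other tests show. Once one arm has been shown non-inferior, at most two null hypotheses can still be true, so the remaining tests need less correction. Holm uses this and needs no assumption beyond those Bonferroni needs. An arm could therefore miss non-inferiority only because the less efficient of two equally protective rules was fixed in advance.

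The second is the power statement. The three tests share Arm C, so their results move together. That raises the chance that all three succeed above what a calculation ignoring the shared control gives. The reported overall power is then not the power of the design.

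Both matter because results for each arm are wanted. The primary hypothesis (Study aim and hypothesis) covers all three alternatives, and the Background asks whether counseling before or after the test is the more important.

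**Working it through.** **Inputs from the article:** margin 4, SD 15.3, one-sided familywise level 0.025, three tests, equal allocation, 1780/4 = 445 per arm (rounded there to 450). **Assumption, not in the article:** the true difference from control is 0 in every arm.

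**1. Per-test power (stated 93%).**
- Standard error = 15.3 × √(2/445) = 1.026.
- Distance of the margin from zero = 4/1.026 = 3.90 standard errors.
- Critical value at 0.025/3 = 0.00833 is 2.394.
- Power = Φ(3.90 − 2.394) = 93.4%. The noncentral t gives 93.3%. With 450 per arm the figures are 93.7% and 93.6%.
- Exactly 93% needs 439 per arm.

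The stated 93% is reproduced.

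**2. Overall power (stated 80%).** Since 80% lies below the 93% for a single test, it cannot be the chance of at least one success. The sensible reading is success in all three. Two simple routes land near it:
- product of independent tests: 0.93³ = 80.4%;
- Bonferroni inequality: 1 − 3 × 0.07 = 79%.

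Neither uses the correlation.

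**3. Correlation from the shared control.** With equal arms, each difference in means has variance 2σ²/n, and any two differences share the control mean's σ²/n. The correlation is (σ²/n)/(2σ²/n) = 0.5.

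**4. Power with that correlation.** The Bonferroni all-three figure at 445 was also obtained from the trivariate normal distribution (84.8%). The other figures come from simulations of 2,000,000 trials. Holm compares the ordered one-sided p-values with 0.025/3 = 0.0083, 0.025/2 = 0.0125 and 0.025, and stops at the first failure.

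| Setting | Quantity | Bonferroni | Holm |
|---|---|---|---|
| Per-test power exactly 93% | all three | 84.0% | 92.5% |
| 445 per arm | all three | 84.8% | 93.0% |
| 450 per arm | all three | 85.4% | 93.4% |
| 445 per arm | average per comparison | 93.4% | 96.5% |
| 445 per arm | at least one | 99.2% | 99.2% |

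At 445 per arm the chance of failing to show all three falls from about 15% to about 7%. Step-down Dunnett gives 93.1% for all three. Single-step Dunnett (critical value 2.349) gives only 86.0%, so most of the gain comes from stepping down and little from using the correlation.

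**5. Error control under Holm.** Simulated familywise error is 0.022 with all three nulls true, 0.023 with two and 0.025 with one, so it stays within 0.025.

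**6. If planning assumptions slip (assumed scenarios).**
- 350 per arm, no true difference: all three 70% under Bonferroni, 84% under Holm.
- 445 per arm, true difference of 1 point in every arm: 47% and 65%.

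**The case against.** The strongest reply is that nothing here is invalid. The 0.025 is split correctly, Bonferroni protects the familywise error under any correlation, the 93% is reproduced, and the planned size exceeds the 439 per arm it needs. All of that stands: the point is about efficiency and reporting.

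Three stronger readings are tempting, and the documents do not support them.

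- **That the trial is underpowered or its overall power overstated.** The opposite holds. On the all-three reading, 80% understates the design's power.
- **That the 80% was computed by assuming independent tests.** The article shows no derivation. The bound of 79% is also close, and it is valid under any dependence. All that can be said is that neither route uses the shared control.
- **That Holm raises power from 80% to 93%.** About 5 points of that gap come from recalculating the existing design (80% to 85%). The procedure itself contributes about 8 points (85% to 93%).

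It can also be said that all-three power is the measure that flatters Holm most, since the arms are tested separately. That is fair. On average per comparison the gain is about 3 points, and on at least one success there is none. But all-three success is the only sensible meaning of the article's own overall power figure, so it is a proper quantity to improve.

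Finally, non-inferiority is often read from a confidence bound. Bonferroni bounds always agree with the Bonferroni decision, whereas Holm has no equally simple matching set. This is a real, though small, cost.

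**Conclusion.** The point holds as an improvement worth making, not as an error in the test. Holm is at least as powerful as the chosen procedure in every case and has the same one-sided familywise level of 0.025. At about 445 per arm it raises the power to show all three arms non-inferior from about 85% to about 93%, and average power per comparison from about 93% to 96.5%. The chance of at least one success is unchanged at about 99%.

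The stated overall power of 80% is conservative and undefined; for the design as written it is about 84% to 85%.

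These figures rest on the protocol's SD and margin, equal evaluable numbers in the four arms (hence the 0.5 correlation), and true differences of 0, which the article does not state. With smaller arms or a small true difference all the powers fall, but Holm's advantage remains.

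**What to change.** Before outcome data are compared by arm:

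1. Replace the fixed 0.0083 for each test with Holm on the ordered one-sided p-values (0.0083, 0.0125, 0.025), stopping at the first that fails. Step-down Dunnett is an alternative with nearly the same power.
2. Define overall power as all three arms being shown non-inferior. Restate it as about 93% for Holm, or about 85% if Bonferroni is kept, naming the zero-difference assumption and the 0.5 correlation.
3. If bounds are wanted, show the one-sided 99.17% Bonferroni bounds (two-sided 98.33% intervals) as supportive. Add a note that an arm can pass Holm while its bound crosses 4 points.

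The cost is a change of wording and a less direct link between decision and interval. It needs no more participants or data and does not raise the error rate.

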## Abstract

**Background:**

Studies have consistently indicated that the majority of individuals meeting the US Prevention Services Task Force guidelines for genetic testing have not had genetic counseling or testing. Despite increased availability and lower costs of multiplex cancer gene panels, there remains a gap in genetics services that has not been addressed by the current care delivery models. Lower cost of DNA sequencing with online patient-initiated ordering could increase test availability, but the ideal quantity and delivery method of patient education is not known. We hypothesized that online genetic education and testing with access to board certified genetic counselors could improve access to genetic testing while maintaining test quality and clinical utility. The MAGENTA (MAking GENetic Testing Accessible) trial is a nationwide randomized study designed to compare the effectiveness of online genetic education with pre- and post-test telephone genetic counseling to three potentially more accessible alternative approaches: online genetic education with optional telephone counseling, online genetic education with required pre-test telephone genetic counseling, and online genetic education with required post-test telephone genetic counseling.

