**Methods:**

3000 women nationwide will undergo genetic testing for 19 hereditary cancer genes. This is a randomized four-arm non-inferiority study with equal randomization. The four study arms were selected to independently assess the delivery of genetic information both before and after genetic testing (pre-test and post-test) by either requiring telephone genetic counseling or providing only online education with optional telephone counseling. Patients have post-test telephone counseling when testing positive for a pathogenic inherited mutation in all four arms. Surveys measuring psychological, behavioral and cognitive state are completed online at baseline, 3 months, 12 months and 24 months post-results disclosure. The primary study outcome is cancer-risk distress at 3 months post-result disclosure.

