One question in this proposed SDM is how much personalized counseling is needed both pre-test and post-test to optimize patient outcomes. Does required personalized counseling reduce patient distress and improve understanding or does it add unnecessary cost and time and reduce likelihood of test completion? Is pre- or post-test counseling more important and if counseling is provided as an option, how many patients will utilize telephone counseling, and can we identify patient subsets who have greater benefit from personalized counseling? To address these considerations, we are conducting a prospective study to evaluate different amount of personalized genetic counseling within an online genetic testing model to determine less counseling is non-inferior to our current accepted SDM at delivering hereditary cancer risk information. The purpose of this paper is to describe the design of the MAGENTA study, a prospective randomized trial of online genetic education vs telephone genetic counseling for hereditary cancer genetic testing.

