## Methods/design

### Study aim and hypothesis

The MAGENTA (MAking GENetic Testing Accessible) trial is designed to compare the effectiveness of pre- and post-test telephone counseling to three potentially more accessible alternatives for individuals undergoing analysis of 19 hereditary breast and ovarian cancer (OC) genes. The genes included are: *ATM, BARD1, BRCA1, BRCA2, BRIP1, CDH1, CHEK2, EPCAM, MSH2, MSH6, MLH1, NBN, PALB2, PMS2, PTEN, RAD51C, RAD51D, TP53,* and *STK11*. Our primary hypothesis is that the outcomes for subjects receiving one of the three alternative approaches utilizing genetic education online will not be inferior to those of participants receiving a current acceptable standard of telephone genetic counseling both pre- and post-testing [4, 5].

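### Both completion tests stop at non-inferiority; a superiority step on the pre-test contrast would answer the article's own question at no alpha cost within that contrast

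*Protocol article*

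**What the plan says.** The Abstract (Methods) describes the design: "This is a randomized four-arm non-inferiority study with equal randomization". Under Study aim and hypothesis, the primary hypothesis is that outcomes in the three alternative arms "will not be inferior to those of participants receiving a current acceptable standard of telephone genetic counseling".

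For completion, Statistical considerations states: "We will test two null hypotheses regarding the completion rate". Both nulls have the same form. The first, for A plus B (online education alone before testing), is that their rate "is more than 6% less than it is for participants who were randomized to receive telephone genetic counseling before testing (Arms C and D"). The second compares arms A and D with "participants who were randomized to receive telephone genetic counseling after testing (Arms B and D"). On the margin the article says: "This 6% non-inferiority margin is more conservative than the 7.5% margin" of an earlier trial. It gives no significance level, power or expected rate for these two tests, and states no superiority test of completion. The regression models in the same section are for scores, so they do not cover completion.

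The motivation is directional. The Abstract (Background) hypothesizes that the online model "could improve access to genetic testing while maintaining test quality and clinical utility". The section on the proposed service delivery model asks of required counseling: "does it add unnecessary cost and time and reduce likelihood of test completion".

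**The concern.** Rejecting either completion null shows that the online-only side is not more than 6% worse. It says nothing formal about a gain, however large the observed difference. The background question runs the other way: does requiring a call cost completed tests?

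A gain is plausible from the design. Under Study design, the saliva kit is mailed only after the pre-test steps are done, so in arms C and D a missed telephone appointment holds up testing. A+B versus C+D is a randomized comparison of exactly that requirement, in large groups. Without a planned step, a claim that required counseling lowers completion would be open to the criticism that it was chosen after the results were seen.

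**Working it through.** **The plan's own figure.** The article gives power only for the distress outcome: 93% per test, with about 450 per arm, SD 15.3, margin 4 and one-sided 0.0083.

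- Power = Φ(4 / (15.3·√(2/450)) − 2.394) = Φ(3.92 − 2.39) = 93.7%.
- With 445 per arm (1780/4) it is 93.4%.
- Overall: 0.93³ = 80.4%.

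The figure reproduces, but it does not bear on completion.

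**Inputs for completion.**
- Size: 3650 randomized women outside the cascade group (Statistical considerations), so about 1825 per pooled pair of arms. Using this group is an assumption, because the completion tests are not expressly limited to it. All 4400 randomized would give 2200 per side.
- Rate: 65%. The article gives this for returning saliva, not for completion, so it is a stand-in. Range used: 50% to 80%.
- Level: one-sided 0.025 per contrast, assumed; 0.0125 shown as the alternative.
- Margin: 6%, read as percentage points.

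**Standard error at equal rates.** √(2·0.65·0.35/1825) = 0.0158, or 1.58 points.

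**Planned non-inferiority test at equal rates.** Φ(0.06/0.0158 − 1.96) ≈ 97% power.

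**Superiority step.** An observed gain of about 1.96·1.58 = 3.1 points would suffice. For a true gain d over a rate p on the telephone side, power = Φ(d/SE − 1.96), with SE = √{[p(1−p) + (p+d)(1−p−d)]/1825}. At p = 0.65:

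| True gain (points) | Power |
|---|---|
| 3 | 48% |
| 4 | 73% |
| 5 | 90% |
| 6 | 97% |

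Gain at which power reaches 80%:

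| Completion, telephone side | Per side | One-sided level | Gain (points) |
|---|---|---|---|
| 65% | 1825 | 0.025 | about 4.4 |
| 80% | 1825 | 0.025 | about 3.6 |
| 50% | 1825 | 0.025 | about 4.7 |
| 65% | 1825 | 0.0125 | about 4.8 |
| 65% | 2200 | 0.025 | about 4.0 |

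**Error rate.** The nulls are nested: a confidence limit above zero is also above −6 points. In 400,000 simulated trials at a true difference of zero (65%, 1825 per side), superiority after non-inferiority was declared in 2.5%. The step therefore costs nothing within one contrast. Across two contrasts at 0.025 each, the familywise rate is 1 − 0.975² ≈ 0.049 if they are independent. The superiority step inherits whatever level is set for the pair.

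**The two contrasts as printed.**
- The post-test contrast names arm D on both sides, while Table 1 gives required post-test counseling to arms B and C.
- Completion is receipt of results under Measure design. Under Statistical considerations it also includes the post-test education or counseling.
- Under the longer definition, arms B and C have a required call to finish that A and D do not. In A+D versus B+C, part of any gain would then be built into the endpoint.
- The pre-test contrast is much less exposed, because each side holds one arm with a required post-test call (B on one side, C on the other).

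**The case against.** A reader might infer that the plan fails to test a hypothesis of its own, namely that dropping required counseling raises completion. The documents do not support that. The Abstract's hypothesis is about access and does not name completion. In the background, access concerns eligible people who never reach testing, whereas completion is measured in women already enrolled and randomized. The sentence on completion is an open question, and the same paragraph turns it into a non-inferiority aim. The planned tests match the stated hypotheses.

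Nor is it right that a gain could not be seen. The interval used for non-inferiority would show one if its lower limit lay above zero, and within a contrast the error rate does not depend on a separate declaration.

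The article is also condensed, and an analysis plan that is not shown may already hold the step. That lowers the weight of the point. It does not remove it, because the article itself says which two completion hypotheses will be tested, and neither answers the question it raises.

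Finally, saying that the step costs no alpha is true only within a contrast, and it would be unsafe to add it to the post-test contrast as printed. Both objections stand and shape the fix.

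**Conclusion.** The point holds as a missed, nearly free improvement, not as a contradiction or an error in the planned tests. The two stated completion tests support only a claim of not more than 6% worse, while the background asks whether required counseling lowers completion. The primary distress analysis is unaffected.

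At the planned size, a superiority step on the pre-test contrast would be well powered for gains of roughly 4 to 5 points. This rests on the assumed group (the 3650 women), on saliva return as a stand-in for completion, and on an assumed level, since the article states none.

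**What to change.** 1. For arms A+B versus C+D, prespecify that once non-inferiority at 6 points is shown, superiority of the online-only side is tested in fixed sequence, at the same one-sided level and from the same confidence interval. Score completion as receiving results, as in Measure design.
2. State the level for the two completion contrasts; the superiority step takes that level.
3. Extend the step to the post-test contrast only after its arms are corrected to A+D versus B+C, in line with Table 1, and completion is scored so that the required post-test call is not part of the endpoint. Table 4 lists giving the results as part of that call, so the definition should say what counts as receiving them in arms B and C.

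The cost is a few sentences, with no further participants or data. The article's data statement says the trial is ongoing with no data available, so at that stage the step could still be prespecified. If an analysis plan already contains it, only the two repairs to the article's text remain.

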### Study design

After online eligibility screening and electronic study consent (as approved by the Human Subjects Division of the MD Anderson Institutional Review Board), randomization into one of four study arms is performed automatically using a web-based data management platform [8]. The four study arms were selected to independently assess the delivery of genetic information both before and after genetic testing (pre-test and post-test) by either telephone genetic counseling or online education alone. The control arm requires mandatory pre and post-test telephone counseling while the other three arms provide various combinations (Table 1). Participants are mailed a saliva collection kit after all pre-test online education and/or genetic counseling is completed, based on study arm. Analysis of 19 OC genes is completed once the participant returns the saliva sample. As an additional safety measure, any participant found to carry a pathogenic or likely pathogenic mutation has required post-test telephone counseling and any participant desiring genetic counseling is provided with telephone genetic counseling regardless of study arm. A study schema can be found in Fig. 1. Participants were stratified into one of two risk groups: individuals with a personal and/or family history of cancer, and those with a known familial mutation (cascade group).

**Table 1 Tab1:** Study Arms

	Pre- Genetic Testing	Post- Genetic Testing
Arm A	Online educational video	Online Test Results Report
Arm B	Online educational video	Online Test Results Report + Telephone Genetic Counseling
Arm C (Control)	Online educational video + Telephone Genetic Counseling	Online Test Results Report + Telephone Genetic Counseling
Arm D	Online educational video + Telephone Genetic Counseling	Online Test Results Report

Note: optional telephone genetic counseling is allowed at any point in all arms at patient request and is mandated post-test for all patients with pathogenic mutation regardless of study arm

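### The two pooled completion tests do not isolate control Arm C, and the second names a comparator that contradicts Table 1; correct it and add arm-versus-control differences

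*Protocol article*

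**What the plan says.** Under Study aim and hypothesis, the Protocol article describes the trial as "designed to compare the effectiveness of pre- and post-test telephone counseling to three potentially more accessible alternatives". The primary hypothesis is that outcomes under the alternatives "will not be inferior to those of participants receiving a current acceptable standard of telephone genetic counseling both pre- and post-testing". That comparator is Arm C: "The control arm requires mandatory pre and post-test telephone counseling while the other three arms provide various combinations" (Study design, Table 1). Measure design lists the testing completion rate among the outcomes used to evaluate the alternative models.

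Study design also gives a factorial rationale: "The four study arms were selected to independently assess the delivery of genetic information both before and after genetic testing".

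Statistical considerations follows the stated aim for the primary outcome, the Impact of Events Scale (IES) score: A, B and D are each tested against C. For completion it follows the factorial rationale: "We will test two null hypotheses regarding the completion rate".

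- Test 1 (pre-test factor): the null for A and B is a completion rate that "is more than 6% less than it is for participants who were randomized to receive telephone genetic counseling before testing (Arms C and D").
- Test 2 (post-test factor): the null has the same form and margin for "the completion rate for the participants receiving only online genetic education after testing (Arms A and D"), with the comparator printed as Arms B and D.

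Each test has its own 6% margin. No significance level, assumed rate or power is stated for completion.

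**The concern.** There are two linked problems.

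- **Wrong arms in test 2.** The comparator is described as the women randomized to telephone counseling after testing. In Table 1 those are Arms B and C. Arm D receives only the online results report after testing, and it already sits in the test group.
- **No completion comparison with Arm C alone.** The comparator in test 1 is half control and half Arm D. With the arms corrected, the comparator in test 2 is half control and half Arm B. Arm A, with neither required call, is the model furthest from the control. A reader who sees both tests pass may conclude that dropping both calls keeps completion within 6 points of the accepted standard. The two tests do not establish that, because each sees only part of the A versus C difference. A loss confined to women who get neither call is halved in each.

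**Working it through.** **The plan's own figure.** The only power figure is for the primary outcome. With 1780/4 = 445 per arm, SD 15.3, margin 4 and one-sided 0.0083, power is 93.4%, and 0.93³ = 80.4%. Both agree with the stated 93% and 80%. There is no completion figure to reproduce.

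**Test 2 as printed.** Letters stand for the arms' completion rates.

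(A + D)/2 − (B + D)/2 = (A − B)/2

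Arm D cancels, and control Arm C does not appear. A 6-point margin on this quantity allows A to be up to 12 points below B. This is not a test of the post-test factor.

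**With the comparator corrected to B and C.**

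(A + B − C − D)/2 + (A + D − B − C)/2 = A − C

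B and D cancel, so no assumption about interaction is needed. Two margins of 6 points bound A − C only at −12. If the two factors act additively, B − C and D − C equal the two marginal differences and are each bounded at −6. Without additivity, neither has a useful bound.

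**How often both tests pass when A is below C.** Inputs:

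- Equal allocation (Abstract, Methods).
- 3650 randomized in the personal or family history group, or 4400 in all (Statistical considerations). This gives 1825 or 2200 per pooled pair, and 912 or 1100 per arm.
- Assumed: completion 65%, taking the plan's saliva-return rate as a proxy, with a range of 55% to 75%.
- Assumed: one-sided 0.025 per test (z = 1.96), and 6% read as percentage points.

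Standard error of a pooled difference: √(2 × 0.65 × 0.35 / 1825) = 1.58 points; with 2200, 1.44 points.

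If A is 6 points below C and the loss is shared equally between the factors, each marginal difference is −3. The halving is the same if the loss is confined to Arm A. The chance that one test passes is Φ((6 − 3)/SE − 1.96):

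- 3650: Φ(1.90 − 1.96) = 0.476
- 4400: Φ(2.09 − 1.96) = 0.550

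The two contrasts are orthogonal, so the chance that both pass is the square of these.

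| True A − C | Both pass, 3650 | Both pass, 4400 | Direct A−C test passes |
|---|---|---|---|
| −6 | 23% | 30% | 2.5% |
| −7.5 | 9% | 12% | about 0.4% |
| −8 | 6% | 8% | about 0.2% |
| −10 | 0.9% | 1.1% | not computed |
| −12 | 0.06% | 0.06% | not computed |

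At −12 each test passes with probability 0.025, and 0.025² = 0.06%. Over 55% to 75% completion, the figure at −6 runs from 20% to 31% (3650) and from 27% to 40% (4400).

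**Power of a direct A−C comparison with no true difference.** SE = √(2 × 0.65 × 0.35 / 912) = 2.23 points; with 1100, 2.03 points.

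- One-sided 0.025: Φ(6/2.23 − 1.96) = 77%; with 1100, 84%.
- One-sided 0.0083 (z = 2.39): 62%; with 1100, 71%.
- For comparison, each pooled test has 97% (3650) to 99% (4400).

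**The case against.** The strongest reply is that the pooled tests are the right ones for a question the plan states. The arms form a 2×2 layout chosen to assess pre-test and post-test delivery separately, and the two tests are its marginal contrasts. The arm-versus-control hypothesis is labelled primary and is carried through for the primary outcome; a secondary outcome may address the other question. This stands. Pooling is not an error, and the pooled tests should stay.

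Nor does the plan say that two passes make Arm A non-inferior to control on completion. The 23% to 30% is therefore not an error rate of any test in the plan: with a true marginal loss of 3 points, each pooled test is right to find the loss within 6. This also stands. The figure measures only how far two passes fall short of supporting a 6-point statement about Arm A.

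Three stronger readings are not supported:

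- A reader might infer that the plan would readily accept an Arm A that is 12 points worse than control. Twelve points is the boundary, and both tests pass there in under 0.1% of trials.
- A reader might infer that the plan's sentence calling 6% more conservative than the 7.5% margin of an earlier trial is wrong. It is correct for each stated test, and the plan makes no such claim for the sum of the two margins.
- A reader might infer that Arm A is likely to lose completers. The Background asks whether required counseling might itself reduce completion, and optional calls remain available in every arm. The direction is open.

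Finally, supplementary pairwise estimates are often left to a full protocol or analysis plan. That tempers the second part of this point. It does not excuse the printed comparator, which contradicts Table 1.

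**Conclusion.** The point holds in a limited form. The comparator printed for the second completion test is a plain contradiction of Table 1 and needs correcting. With it corrected, both tests are legitimate tests of the two factors, but neither isolates Arm C, and passing both does not show that Arm A is within 6 points of control. Both would pass in about 23% to 30% of trials at a true 6-point deficit and in about 9% to 12% at 7.5 points. These figures rest on 65% completion, one-sided 0.025 per test and 3650 to 4400 randomized women; the rate and the level are assumptions, since the article states neither for completion. The identity between the two contrasts and A − C rests on no assumption beyond reading the second comparator as B and C.

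**What to change.** In Statistical considerations:

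- Correct the comparator of the second completion test to Arms B and C.
- Keep both pooled tests with their 6% margins.
- Add the completion differences A−C, B−C and D−C with confidence intervals, among all randomized women.
- State that any completion claim for Arm A versus control rests on the A−C interval against the 6-point margin, and not on both pooled tests passing.
- Leave the sentence on the 7.5% margin as it is.

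The cost is a few lines of text, with no new patients or data. The downside is lower power for A−C than for a pooled test: about 77% to 84% at one-sided 0.025, or about 62% to 71% if the plan's three-test correction (0.0083) is applied, so the level should be stated with the comparison.
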